#### Sample size

2.5.2

Based on the PASI scores, the published study reported that the total curative rate in the acupuncture group was 97.5%, and 87% in the control group.^[20]^ In the current study, we assumed that a significance level α was 0.05 and a power (1-β) = 0.80, and calculated the sample size: 88 participants with psoriasis would be required in each group for 80% power to detect a difference between manual acupuncture group and sham acupuncture group using the two-sided Z test with pooled variance. The significance level of the test is 0.05. Given a 20% loss to follow-up, therefore this study will require at least 220 participants.

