#### Primary outcomes

2.4.1

The primary outcome of the current study is the proportion of patients with a reduction in the Psoriasis Area and Severity Index (PASI) scores ≥50% compared with baseline. PASI score will be evaluated at the same or closet day. Target lesions will be recorded as digital photographs by single-lens reflex cameras during each session.

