## Discussion

3

As a chronic, inflammatory, immune-mediated skin disease, psoriasis is characterized by frequent relapses.^[21]^ It usually requires combination medicines for alleviating rash in the clinic, but this does not always result in satisfactory long-term effects. The studies shown that the 48-week recurrence rate in patients treated with ixekizumab was as high as 87%,^[22]^ 3-month recurrence rate in patients treated with brodalumad (an interleukin-17 targeted biological) was 78%,^[23]^ 4-month recurrence rate in patients treated with narrow-spectrum ultraviolet B was 54.55%.^[24]^ Therefore, there is increasing concern regarding the complementary and alternative medicine in the modern practice of various dermatology.

According to the theory of traditional Chinese medicine, psoriasis should be mostly a “blood stasis” syndrome. Acupuncture may promote blood circulation, remove blood stasis, and regulate qi and blood circulation. The studies showed that acupuncture have beneficial effects for the treatment of plaque psoriasis.^[13,25]^ Although the mechanism of acupuncture for psoriasis is not clear, there are indications that acupuncture combined with other treatments, including western medicine, phototherapy, and so on, can alleviate plaque psoriatic skin inflammation and excessive thickening of skin lesions.^[26]^ However, the effect of acupuncture alone for psoriasis is less evaluated especially comparing with sham acupuncture. In addition, psoriasis may also be associated with psychological disorders.^[27]^ It seriously affects the quality of life and is an economic burden to the patient. Previous studies reported that acupuncture showed a potential advantage in the management of anxiety and depression.^[11,12]^ Therefore, the current study will evaluate the effect of manual acupuncture in the management of psoriasis without the compounding interference of combination treatment strategies.

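### The planning rates are not shown to be PASI-50 rates against sham, so the stated 80% power is unsupported for the primary comparison, in a direction the protocol does not settle

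*Protocol article*

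**What the plan says.** Section 2.5.2 (Sample size) takes its planning rates from one cited study: "Based on the PASI scores, the published study reported" that "the total curative rate in the acupuncture group was 97.5%, and 87% in the control group". It sets "a significance level α was 0.05 and a power (1-β) = 0.80" and concludes that "88 participants with psoriasis would be required in each group for 80% power" are needed "to detect a difference between manual acupuncture group and sham acupuncture group", "using the two-sided Z test with pooled variance". A 20% allowance for loss brings the total to 220.

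Section 2.4.1 defines the primary outcome as "the proportion of patients with a reduction in the Psoriasis Area and Severity Index (PASI) scores ≥50% compared with baseline".

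The Discussion (Section 3) remarks that "the effect of acupuncture alone for psoriasis is less evaluated especially comparing with sham acupuncture".

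**The concern.** Two links are missing between the planning rates and the trial.

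- **Endpoint.** A curative rate based on PASI could use any cut-off. The article does not say that it was a 50% reduction.
- **Comparator.** The cited study's control is not described, yet its 87% becomes the response rate under sham needles. The Discussion itself describes the sham evidence as thin.

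The borrowed 87% also needs explaining in its own right. Under Sections 2.2.2 and 2.2.3, participants go without other treatment from three weeks beforehand and without other active interventions during the trial. Used as a sham PASI-50 rate, 87% means that almost nine in ten of them halve their PASI. It leaves 13 points of room for improvement, of which the assumed effect takes 10.5.

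At stake is what the trial can be said to detect. If the two rates do not describe PASI-50 against sham, the 80% figure tells a reader nothing about the primary comparison, and a non-significant result could not be weighed against it.

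**Working it through.** **Inputs (Section 2.5.2).** p1 = 0.975, p2 = 0.87, difference d = 0.105, two-sided α = 0.05 (z = 1.960), power 0.80 (z = 0.842), pooled-variance Z test, 88 per arm. Allocation is 1:1 (Section 2.2.5).

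**Formulae.** With p̄ = (p1 + p2)/2:

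- n per arm = [1.960·√(2p̄(1−p̄)) + 0.842·√(p1(1−p1) + p2(1−p2))]² / d²
- power = Φ{[d√n − 1.960·√(2p̄(1−p̄))] / √(p1(1−p1) + p2(1−p2))}

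**Step 1: the plan's own figure.** p̄ = 0.9225, √(2p̄(1−p̄)) = 0.3781 and √(0.0244 + 0.1131) = 0.3708.

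- n = (1.960 × 0.3781 + 0.842 × 0.3708)² / 0.105² = (1.0532/0.105)² = 100.6, so 101 per arm. The stated 88 is not reproduced.
- Power with 88 per arm is Φ(0.658) = 74.5%. With 110 per arm it is Φ(0.971) = 83.4%.
- Exact enumeration of the pooled Z test gives 77.7% with 88 per arm and first reaches 80% at 93.
- Of the variants tried, only the arcsine formula comes close (88.9), and it is not the method named.
- The loss step does reproduce: 88/0.8 = 110 per arm, 220 in total. From 101 per arm it would be 127 per arm, 254 in total.

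**Step 2: other sham rates.** The documents give no PASI-50 rate under sham, so the sham rate is an assumption, shown over a range. The scale on which the effect carries over is also an assumption, so both versions are shown. The odds ratio implied by the planning rates is (0.975/0.025)/(0.87/0.13) = 39.0/6.69 = 5.83. The fourth column is the difference detectable with 80% power at 88 per arm.

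| Sham rate | Power, 88/arm, 10.5 points | n/arm for 80%, 10.5 points | Detectable difference (points) | Active rate at OR 5.83 | Power, 88/arm, OR 5.83 |
|---|---|---|---|---|---|
| 10% | 49% | 183 | 16 | 39.3% | above 99% |
| 20% | 36% | 268 | 19 | 59.3% | above 99% |
| 30% | 31% | 324 | 21 | 71.4% | above 99% |
| 50% | 29% | 351 | 21 | 85.4% | above 99% |
| 70% | 36% | 264 | 17 | 93.1% | 98% |
| 80% | 50% | 178 | 14 | 95.9% | 91% |
| 87% | 74.5% | 101 | 11 | 97.5% | 74.5% |

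**Step 3: the floor.** Binomial variance is symmetric about 50%. Rates of 2.5% and 13% give the same variance as 87% and 97.5%, and hence the same 74.5% power with 88 per arm. A sham rate near zero is therefore as favourable to a 10.5-point difference as one near 87%.

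**The case against.** The strongest reply is that the rates may be exactly what the trial needs. They are introduced as PASI-based, the cited study is not at hand, and its threshold could be 50% and its control sham. The Discussion's remark says that sham comparisons are few, not that none exist. This stands. A reader might infer that the rates are not PASI-50 rates against sham, but the document supports only that they are not shown to be.

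A second reply concerns the low power figures. A reader might infer from them that the trial is badly underpowered unless the sham rate is near the ceiling. That does not follow, for two reasons. A sham rate near the floor is just as favourable. And the low figures hold only if the absolute difference stays at 10.5 points; Section 2.5.2 gives two rates and never names 10.5 points as the target. Carrying over the odds ratio turns the same sham rates into powers of about 91% or more.

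A third reply is that no passage commits the authors to reading a non-significant result as absence of effect. That too is right, so misreading is a risk and not something the plan prescribes.

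None of these replies supplies the missing link between the cited rates and the primary comparison, and none rescues 88 per arm under the named test. Nor is this mere condensation in a journal article: the rates, test, sample size and power are all stated outright.

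**Conclusion.** The point holds in a limited form. The 80% power rests on two borrowed rates whose response threshold and comparator are not given, so it is not shown to apply to PASI-50 against sham. The direction of the error cannot be determined from the document: at assumed sham rates of 10% to 80%, power with 88 per arm runs from about 29% to above 99%, depending on whether the absolute difference or the odds ratio is held fixed.

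One part needs no assumption about the sham rate. On the article's own rates and named test, 88 per arm gives 74.5% by the normal approximation (77.7% by exact enumeration), not 80%. If all 110 per arm contribute to the analysis, power at those rates is 83.4%. The shortfall there is modest, but the statement has to be reworded in any case.

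**What to change.** Keep 220 participants and revise Section 2.5.2 as follows.

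- Remove the claim of 80% power with 88 per arm.
- State the response threshold and the comparator behind the cited 97.5% and 87%. If they do not correspond to PASI-50 and sham, or this cannot be established, say plainly that the match is an assumption.
- Tabulate the difference detectable with 80% power at 88 per arm by sham rate: about 16 points at 10%, 19 at 20%, 21 at 30% to 50%, 17 at 70%, 14 at 80% and 11 at 87%.

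The cost is wording and one small table, with no added participants. The downside is that the stated power becomes less favourable.

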#### Randomization and allocation

2.2.5

The participants will be randomly assigned to manual acupuncture group or sham acupuncture group at a 1:1 ratio after the baseline assessment. The randomization list will be generated using the Statistical Analysis Software (9.1) by a research assistant who is not involved in the recruitment of participants. The sealing and opaque envelopes will be used to achieve the allocation concealment.

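### The 88 per group stated for 80% power does not follow from 97.5% vs 87% with the named pooled Z test, which needs 101 by formula or 93 by exact calculation

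*Protocol article*

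**What the plan says.** Section 2.5.2 of the protocol article contains the whole sample size argument.

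- **Rates.** From a published study, "the total curative rate in the acupuncture group was 97.5%, and 87% in the control group".
- **Error rates.** The assumptions are "a significance level α was 0.05 and a power (1-β) = 0.80".
- **Result.** The section concludes that "88 participants with psoriasis would be required in each group for 80% power to detect a difference" between the two arms, "using the two-sided Z test with pooled variance".
- **Loss.** "Given a 20% loss to follow-up, therefore this study will require at least 220 participants".

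Two other sections supply the rest. Under Randomization and allocation (2.2.5), participants are "randomly assigned to manual acupuncture group or sham acupuncture group at a 1:1 ratio". Under Primary outcomes (2.4.1), the endpoint is binary: "the proportion of patients with a reduction in the Psoriasis Area and Severity Index (PASI) scores ≥50% compared with baseline". No other rate, effect size or formula appears in the article.

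**The concern.** Two rates, a two-sided alpha, a power, an allocation ratio and a named test determine the sample size, apart from the choice between normal approximation and exact calculation. The stated 88 can therefore be checked without the cited study, and it is below the result on either calculation.

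Section 2.5.2 is the only justification given for 220 participants. If 88 evaluable per group is too few for the assumed effect, the trial carries a higher chance of missing that effect than the 20% it declares, at the retention it plans for. A reader also cannot tell whether the number, the rates or the description of the test is at fault.

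**Working it through.** **Inputs.** p1 = 0.975, p2 = 0.87, difference 0.105, two-sided alpha 0.05 (z = 1.960), power 0.80 (z = 0.8416) and the pooled Z test, all from section 2.5.2. Allocation is 1:1 (section 2.2.5). The pooled rate is (0.975 + 0.87)/2 = 0.9225.

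**Loss step, as stated.** 88/(1 − 0.20) = 110 per group, 220 in total. This step reproduces.

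**Named test, standard formula.**

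n = [1.960 × √(2 × 0.9225 × 0.0775) + 0.8416 × √(0.975 × 0.025 + 0.87 × 0.13)]² / 0.105²

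- First term: 1.960 × √0.1429875 = 0.7411
- Second term: 0.8416 × √0.137475 = 0.8416 × 0.3708 = 0.3121
- Sum squared: 1.0532² = 1.1092
- n = 1.1092/0.011025 = 100.6, so **101 per group**, 13 more than 88

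**Named test, exact calculation.** Here the binomial probabilities of all pairs of response counts at which the two-sided pooled Z statistic reaches 1.960 are summed. Power is 79.9% at 92 per group and 80.4% at 93. The requirement is **93 per group**, 5 more than 88.

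**Power at given sizes.** By formula, power = Φ[(0.105√n − 0.7411)/0.3708].

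- n = 88: (0.9850 − 0.7411)/0.3708 = 0.658, so 74.5%
- n = 110: (1.1012 − 0.7411)/0.3708 = 0.971, so 83.4%

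| Evaluable per group | Formula | Exact |
|---|---|---|
| 88 (220 randomised, 20% loss) | 74.5% | 77.7% |
| 110 (220 randomised, no loss) | 83.4% | 87.5% |

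The shortfall at 88 is 80 − 74.5 = 5.5 points by formula and 80 − 77.7 = 2.3 points exactly.

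**Loss that 220 can absorb.** 1 − 101/110 = 8.2% by formula; 1 − 93/110 = 15.5% exactly.

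**Search for the origin of 88.** Other calculations with the stated rates, per group:

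| Method | n |
|---|---|
| Unpooled formula | 98 (97.9) |
| Continuity-corrected pooled formula | 119 |
| One-sided pooled formula | 80 |
| Arcsine formula | 88.9, so 89 |
| Exact enumeration of the unpooled Z test | 89 (79.8% power at 88) |

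Only the last two come close, and the text names neither. Changing the rates slightly also comes close. With a control rate of 86.6%, exact enumeration of the pooled Z test gives 79.6% power at 87 and 80.1% at 88, hence 88. The standard pooled formula still gives 95 at a control rate of 86.5%.

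**The case against.** **The normal approximation is rough here.** With 88 per group at 97.5%, about 2 failures are expected in the acupuncture arm (88 × 0.025 = 2.2). The exact figure is then the better guide, and the deficit is 2.3 points and 5 participants per group. This stands, and it is why both figures are reported. It does not rescue 88, because the exact calculation also falls short.

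**The control rate may be rounded.** It is printed without a decimal, whereas 97.5% has one, and a value near 86.6% would give exactly 88 by enumeration. This is possible but cannot be confirmed from the article. If it is the explanation, the text should give the unrounded rate and say that the calculation was exact.

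**The power may be adequate in practice.** Section 2.5.1 specifies intention-to-treat, and section 2.6 says the researchers will try to obtain last-evaluation data for that analysis. With all 110 per arm analysed at the assumed rates, power is above 80% on both calculations. A reader might infer that the trial as sized is underpowered outright; the documents do not support that. The shortfall arises at the plan's own allowance of 20% loss.

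**Two further readings go too far.**

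- A reader might take the power of Fisher's exact test (69% at 88 per group) as the true figure. Section 2.5.1 lists it only as an alternative to chi-squared. The expected number of failures under the null is 88 × 0.0775 = 6.8 per arm, above the usual small-count threshold of 5, so chi-squared, which is equivalent to the pooled Z test, would normally apply.
- A reader might count every lost participant as a non-responder and arrive at a far lower power. The article states no such rule, and a rule for missing outcomes may properly sit in an analysis plan that is not shown.

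**Conclusion.** The stated figure is wrong as written. For 97.5% vs 87%, two-sided alpha 0.05 and the pooled Z test, 80% power needs 101 evaluable per group by the standard formula or 93 exactly, not 88. At the plan's own design point the chance of missing the assumed effect is 22.3% (exact) to 25.5% (formula) instead of 20%. The loss inflation is correct in itself but starts from a number that its inputs do not support.

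This rests on taking the printed rates and the named test at face value and on losing the full 20% from the analysis. It is a modest error in the power statement that should be corrected. It does not invalidate the design, the endpoint or the choice of test, and it does not by itself call for more participants.

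**What to change.** Either of two corrections to section 2.5.2 would do.

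1. **Keep 220 and restate the figures**, for example: for 97.5% vs 87%, two-sided alpha 0.05 and the pooled Z test, 101 evaluable participants per group (93 by exact calculation) are needed for 80% power; 220 randomised with 20% loss gives about 74% power (normal approximation) to 78% (exact), and 80% is reached if loss is at most about 8% (approximation) or 15% (exact).
2. **State what produced 88**: the actual method and the unrounded rates, with the description of the test corrected if it was not the pooled Z test.

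Both cost only wording. The first makes the declared power slightly less favourable; neither changes recruitment.

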### Quality control and safety monitoring

2.6

In order to complete the trial with high quality, the recruitment must be strictly in accordance with the inclusion/exclusion criteria of the trial protocol. The participants must be randomly grouped using allocation sequence generated by the software statistical analysis software 9.1. The participants are free to withdraw from this trial at any time for any reason to ensure data authenticity and credibility. Of cause, the researchers will try their best to get the data of last evaluation for an intention-to-treat analysis.

The acupuncturists are graduated from acupuncture and moxibustion major in the University of Traditional Chinese Medicine, who are trained in aseptic acupuncture procedures again. The researchers will document, report and analysis any adverse event including subcutaneous hematoma, fainting, and so on during every session. Before and after the study, all participants will receive liver and kidney function examinations, routine blood texts, and stool tests to exclude severe heart/liver/kidney diseases and evaluate possible side effects of the acupuncture.

## Discussion

3

As a chronic, inflammatory, immune-mediated skin disease, psoriasis is characterized by frequent relapses.^[21]^ It usually requires combination medicines for alleviating rash in the clinic, but this does not always result in satisfactory long-term effects. The studies shown that the 48-week recurrence rate in patients treated with ixekizumab was as high as 87%,^[22]^ 3-month recurrence rate in patients treated with brodalumad (an interleukin-17 targeted biological) was 78%,^[23]^ 4-month recurrence rate in patients treated with narrow-spectrum ultraviolet B was 54.55%.^[24]^ Therefore, there is increasing concern regarding the complementary and alternative medicine in the modern practice of various dermatology.

According to the theory of traditional Chinese medicine, psoriasis should be mostly a “blood stasis” syndrome. Acupuncture may promote blood circulation, remove blood stasis, and regulate qi and blood circulation. The studies showed that acupuncture have beneficial effects for the treatment of plaque psoriasis.^[13,25]^ Although the mechanism of acupuncture for psoriasis is not clear, there are indications that acupuncture combined with other treatments, including western medicine, phototherapy, and so on, can alleviate plaque psoriatic skin inflammation and excessive thickening of skin lesions.^[26]^ However, the effect of acupuncture alone for psoriasis is less evaluated especially comparing with sham acupuncture. In addition, psoriasis may also be associated with psychological disorders.^[27]^ It seriously affects the quality of life and is an economic burden to the patient. Previous studies reported that acupuncture showed a potential advantage in the management of anxiety and depression.^[11,12]^ Therefore, the current study will evaluate the effect of manual acupuncture in the management of psoriasis without the compounding interference of combination treatment strategies.

### Limitation

3.1

There still are limitations in the current study. First, it will be impossible to blind the therapists due to the characteristics of acupuncture interventions. In order to minimize the risk of detection bias, all results will be assessed by independent researchers. Second, small deviations in the manipulation of acupuncture therapy and locations of acupoints are inevitable, but performance bias can be reduced through unified professional training for acupuncturists. Third, patients choosing alternative therapies may be inclined to choose manual acupuncture treatment, which result in allocation bias during recruiting patients for the sham acupuncture group. In conclusion, this study aims to verify whether manual acupuncture therapy is effective for psoriasis. We also hope to provide a safe and effective treatment for psoriasis through this study.
